#### Secondary analyses

The explanatory outcomes are the patients’ compliance with the training, and their satisfaction with the exercise program will be analyzed using quantitative and qualitative methods, depending on the level of the data. All these analyses will be described in more detail in the statistical analysis plan in a separate document after the finalization of the protocol.

#### Safety analysis

All adverse and serious adverse events that are recorded during the study will be described with regards to their severity grade, relationship to the COPD app intervention, and duration. The occurrence of adverse events and AEs overall between groups will be assessed with a two-tailed *t* test after the end of the follow-up.

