### Trial design {8}

This trial is an international, multicenter, parallel-group, randomized, controlled study. Study participants are stage II–IV COPD patients who will be randomly assigned to the intervention group that will be provided with the KAIA COPD app or to a control group that will receive usual care. In total, 104 participants will be randomized (52 participants will be allocated to the intervention group and 52 to the control group). Two centers specializing in inpatient PR for COPD (Schoen Klinik Berchtesgadener Land, Germany and Zuercher RehaZentren Klinik Wald, Schweiz) will recruit study participants.

The estimated duration of the main study phase is planned to last approximately 1.5 years. All potential participants are COPD patients who are taking part in a regular inpatient PR program. The study started with screening of the first participant in August 2019. Enrollment of participants in the study is planned for a 12-month period. The last patient to complete the program is expected to finish in February 2021.

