#### Criteria for discontinuing or modifying allocated interventions {11b}

Each participant will be informed that participation in the study is voluntary, that he/she may withdraw from the study at any time, and that withdrawal of consent will not affect his/her subsequent medical assistance and treatment. The study might be prematurely terminated due to ethical concerns or insufficient participant recruitment or when the safety of the participants is doubtful or at risk, when alterations in accepted clinical practice make the continuation of a clinical trial unwise or when there is early evidence of benefit or harm of the experimental intervention.

For participants who prematurely stop the study, follow-up assessments that are normally conducted during visits 5 and 8 will be conducted at the point of termination only if the participants agree.

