### Participant timeline {13}

The study will take approximately 1.5 years to completion. The screening period is scheduled after a minimum of 7 days and a maximum of 14 days during inpatient rehabilitation. Once the participant enters the study and is randomized, the treatment period lasts for 6 months with biweekly follow-up for SAEs/AEs and device deficiencies. Any participant who is not responding to the visit emails will be followed up with 3 times until being considered lost to follow up. Figure 2 displays the study schedule in detail.

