### Sample size {14}

In total, 104 participants are expected to be recruited, 52 for the intervention group and 52 for the control group each. The sample size calculation is based on the primary outcome, the difference between groups in the average steps per day within 1 week at the 6-month follow-up. As this study had no pilot study, there are no further statistical sample size considerations. The well-established minimally important difference in steps per day after pulmonary rehabilitation lies between 600 and 1100 steps as measured with an activity tracker during an intervention. Assuming a standard deviation of the outcome variable of 2500 steps/day, an expected effect size of 2000 steps/day can be assumed for programs combining physical activity counseling with PR to increase activity, according to current meta-analyses. To achieve 80% power and a significance level of 5% (one-sided), a sample size of 26 patients in each group is required, which results in a total sample size of 104, assuming a drop-out rate of 50%. The sample calculation is based on a one-tailed nonpaired *t* test comparing the two groups with each other at the final visit at the end of the follow-up period.

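### The between-arm adverse event test ignores follow-up time, so unequal drop-out could hide or falsely create an excess of events

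*Protocol article*

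**What the plan says.** The Safety analysis section has two parts. The first is descriptive: "All adverse and serious adverse events that are recorded during the study will be described with regards to their severity grade", together with relationship to the app and duration. The second is a test: "The occurrence of adverse events and AEs overall between groups will be assessed with a two-tailed" t test, carried out after follow-up ends. The section does not say whether the variable is patients with an event or events per patient. It has no person-time term. It names adverse events twice, where AEs and SAEs were apparently meant.

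Other sections determine how long each patient is observed:

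- Trial design {8}: "52 participants will be allocated to the intervention group and 52 to the control group".
- Participant timeline {13}: "the treatment period lasts for 6 months with biweekly follow-up for SAEs/AEs and device deficiencies", and "Any participant who is not responding to the visit emails will be followed up with 3 times until being considered lost to follow up".
- Criteria for discontinuing {11b}: after an early stop, "follow-up assessments that are normally conducted during visits 5 and 8 will be conducted at the point of termination only if the participants agree".
- Sample size {14}: the total is set "assuming a drop-out rate of 50" per cent, one pooled figure not split by arm.

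**The concern.** If the plan's own drop-out assumption is right, about half the patients may have AE observation shorter than 24 weeks. The stated test counts a patient observed for 4 weeks and one observed for 24 weeks alike. The arm observed for less time has less opportunity to record events and so looks safer.

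Unequal drop-out is plausible here. The trial is open label. Only app patients have daily sessions and are telephoned when they train on fewer than 4 of 7 days (Intervention description {11a}). Controls are offered the app free once they finish (Explanation for the choice of comparators {6b}). These features could push retention either way. What is at stake is whether the between-arm safety result reflects event rates or length of observation.

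**Working it through.** **The plan's own figure.** No number is given for the safety comparison. The drop-out allowance reproduces: 26 / (1 − 0.5) = 52 per arm, 104 in total.

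**Inputs from the protocol article.** 52 per arm; 24 weeks; AE contact every two weeks; 50% drop-out overall.

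**Assumptions, not in the documents.** Exit times uniform over 24 weeks; drop-out by arm varied around an overall 50%; AE counts overdispersed (gamma frailty variance 1); control mean between 0.5 and 4 AEs per 24 weeks; constant event rate over time.

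**Step 1: mean exposure.** With drop-out proportion d, mean exposure = 24(1 − d) + 12d weeks.

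- d = 0.3: 20.4
- d = 0.4: 19.2
- d = 0.5: 18.0
- d = 0.6: 16.8
- d = 0.7: 15.6

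**Step 2: bias in the ratio of mean counts.** Apparent ratio = true rate ratio × (app exposure / control exposure).

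- Control/app 50/50: 18.0 / 18.0 = 1.00, no bias.
- 40/60: 16.8 / 19.2 = 0.875. A true ratio of 19.2 / 16.8 = 1.143 appears as 1.00, and a true 2.0 appears as 1.75.
- 30/70: 15.6 / 20.4 = 0.765. A true ratio of 20.4 / 15.6 = 1.308 appears as 1.00, a true 1.5 as 1.15 and a true 2.0 as 1.53.
- 70/30: equal true rates appear as 1.31, a false excess in the app arm.

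**Step 3: false rejection with equal true rates** (simulation, 52 per arm, two-sided 5% t test on counts). With 50/50 drop-out, about 5%. With 40/60, about 7 to 9%. With 30/70, about 14 to 19%, or 10 to 16% if AEs are less frequent (control mean 0.5 to 2 per 24 weeks). In the 40/60 and 30/70 settings nearly all rejections favour the app.

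**Step 4: power at a true rate ratio of 2** (control mean 1 AE per 24 weeks; 20,000 trials per setting).

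| Control/app drop-out | t test on counts | t test on any AE | Exposure-adjusted rate ratio |
|---|---|---|---|
| 50/50 | 61% | 36% | 68% |
| 40/60 | 42% | 22% | 68% |
| 30/70 | 26% | 12% | 68% |

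The rate-ratio test (robust standard error) has a type I error of about 5.4 to 6.2%.

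**Step 5: is the t test itself at fault?** On yes/no occurrence at 52 per arm, exact enumeration gives a t test size of 0.2 to 4.4% at event rates of 1 to 5%, and 4.9 to 5.2% at 10 to 50%. On overdispersed counts with equal follow-up its size is 4.8 to 5.0%. It does not over-reject materially in these settings.

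**The case against.** **The imbalance is assumed.** This stands. The article gives one pooled drop-out figure, used to size the primary outcome. With equal drop-out the ratio of mean counts is unbiased, and power falls only from 68% to 61% in the case above. A reader might infer that 50% drop-out by itself hides harm in the app arm. The documents do not support that: the bias needs unequal drop-out, and its direction is unknown.

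**The t test is not badly behaved.** This also stands. A reader might infer that it overstates significance for rare events, pointing to 0/52 against 4/52, where it gives p = 0.042 and Fisher's exact test 0.118. Pearson's chi-square gives 0.041 for the same table; the gap reflects Fisher's conservatism. Changing to chi-square or Fisher would leave the exposure problem untouched, and Fisher would lose power: for 5% against 20%, 53.4% against 66.6% for the t test.

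**Follow-up need not stop at withdrawal.** Partly right. The retention section {18b} offers the usual follow-up after withdrawal where feasible and agreed, and detected events are followed to resolution {22}. Neither guarantees that new events are captured for 24 weeks. The last-value rule for missing V8 assessments does not restore unobserved AE time.

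**Descriptive tables will show the events.** True, so the events themselves would not be concealed. But severity, relationship and duration do not adjust for exposure.

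**Serious events.** A reader might infer that SAEs have no comparison at all. That goes too far: SAEs are a subset of AEs and are described separately. The duplicated term is an editorial slip.

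**The SAP may settle it.** An SAP may exist, but this section names its own test, and the article requires deviations from the statistical plan to be reported to the ethics committee and justified. It is a stated choice, not an omitted detail.

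**Conclusion.** The point holds in a limited form. The article commits to a between-arm AE comparison that ignores follow-up time in a trial planned with 50% drop-out and with AE observation that can end early. If drop-out differs by arm, the result can be wrong in either direction. A 20-point difference in drop-out masks or mimics a rate difference of about 14%, and a 40-point difference one of about 31%. These sizes rest on uniform exit times, a constant AE rate and the assumed splits; the rejection rates also depend on the assumed AE frequency and overdispersion. If drop-out turns out equal, the consequence is only a modest loss of power. The correction is worth making before analysis because it is cheap and protects against an imbalance that cannot be known in advance.

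**What to change.** In the Safety analysis section, and in the SAP if it repeats the test:

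1. Replace the t test by AE and SAE rates per patient-week, compared by a rate ratio with confidence interval from a negative binomial (or robust Poisson) model with log follow-up time as offset. Report total and mean exposure by arm.
2. As a supplement, show by arm the number of patients with at least one AE and with at least one SAE, with a risk difference and confidence interval. These figures also ignore exposure, so neither they nor Fisher's test should be the main comparison.
3. Replace the duplicated mention of adverse events by the intended terms, apparently AEs and SAEs.

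The cost is minor programming, the derivation of each patient's last safety contact date from the two-weekly follow-up, and reporting of the change as the article requires. The offset corrects for unequal observation time. It does not fully correct for patients who leave because of an adverse event, so reasons for leaving should be shown by arm.

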### Deviation(s) from the original statistical plan

Deviations from the intended statistical plan will be reported to the responsible ethics committee before implementing them, and potential amendments in the protocol will be made. They will furthermore be justified and listed in the final report.

### Handling of missing data and drop-outs

As described above, the main analyses will be conducted with an intention-to-treat approach, and missing follow-up data for patients who do not complete the V8 assessments will be substituted with baseline assessment data or the last known data (i.e., last outcome carried forward).

### Interim analyses {21b}

#### There are no anticipated problems that will be detrimental to the participant

##### Methods for additional analyses (e.g., subgroup analyses) {20b}

Additional analyses are planned according to COPD stage, age, comorbidities, and 6-MWT at discharge from PR.

##### Methods in the analysis to handle protocol nonadherence and any statistical methods to handle missing data {20c}

Missing follow-up data for patients who do not complete the V8 assessments will be substituted with the last available measurement (i.e., last outcome carried forward).

##### Plans to give access to the full protocol, participant level-data, and statistical code {31c}

The datasets analyzed during the current study will be available from the corresponding author on reasonable request.

### Oversight and monitoring

#### Composition of the coordinating center and trial steering committee {5d}

The principal investigator is responsible for all aspects of local organization, including identifying potential recruits and obtaining consent. She or he will also supervise the trial and how often the local investigator team meets. The Trial Steering Committee (TSC) is composed of the two principal investigators and the sponsor medical lead. They will meet over the course of the trial at least bimonthly to oversee the conduct and progress of the trial. There is not a plan to integrate a public reference group due to the design of the study.

#### Composition of the data monitoring committee and its role and reporting structure {21a}

A data monitoring committee will not be assembled; however, monitoring will be carried out by the assigned clinical study monitor from the sponsor. One regular monitoring visit organized by the sponsor will be planned at the investigator sites prior to the start and during the course of the study. All collected source data and other documents will be monitored.

During monitoring, the internal monitor will check the completeness of patient records, the accuracy of entries on the eCRFs, the adherence to the protocol regarding the assessments and Good Clinical Practice guidelines, and the progress of enrollment. Internal monitoring will be conducted according to a detailed monitoring plan.

### Adverse event reporting and harms {22}

Adverse events (AEs) are defined as any untoward medical occurrence in a patient or clinical investigation participant after the intervention which does not necessarily have a causal relationship with the treatment. An AE can therefore be any unfavorable and unintended sign (including an abnormal laboratory finding), symptom, or disease temporally associated with the intervention, whether or not related to the intervention. An AE may also consist of a new disease, an exacerbation of a pre-existing illness or condition, a recurrence of an intermittent illness or condition, a set of related signs or symptoms, or a single sign or symptom.

Serious adverse event

A serious adverse event is defined as any event that
Requires inpatient treatment not envisaged in the protocol or extends a current hospital stay;Results in permanent or significant incapacity or disability;Is life-threatening or results in death; orCauses a congenital anomaly or birth defect.

All serious adverse events that occur after visit 1 will be collected in the eCRF. Medical conditions/diseases present before starting the study are only considered adverse events if they worsen after starting the study. Directly after registration, AEs and SAEs are judged by the PI to be related/not related or probably related to the intervention.

Adverse events occurring during the study will be recorded on the Adverse Events eCRF with the following information:
The severity grade (mild, moderate, severe)The relationship to the KAIA COPD app intervention (suspected/not suspected)The duration (start and end dates)

Once an adverse event is detected, it will be followed until its resolution or until it is judged to be permanent, and an assessment will be made at each contact (or more frequently, if necessary) of any changes in severity, the suspected relationship to the intervention, the interventions required to treat it, and the outcome.

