**Methods:**

This is the protocol for a randomized, controlled, open-label, multicentered trial that will be carried out at inpatient PR hospital centers in Germany and Switzerland. The interventions will involve the use of the KAIA COPD app program (Arm 1) or an active comparator, i.e., usual care (Arm 2). Patients completing an in-hospital PR program and consenting to participate in the study will be screened with the inclusion and exclusion criteria and enrolled in the study. After fulfilling the screening requirements, the patients will be randomized into one of the two arms with parallel group assignment in a 1:1 ratio. The training program will be delivered to the participants grouped in Arm 1 via the KAIA COPD app and to participants grouped in Arm 2 via the regular recommendations or standard of care by the PI. In total, 104 participants will be included in the trial. The treatment period will last for 24 weeks. Electronic versions of questionnaires will be used to collect patient-reported assessments remotely. The primary outcome measure is the change in physical activity of the intervention group in comparison to the control group, measured over 1 week as the mean steps per day with a Polar A 370 activity tracker, from baseline (end of PR) to the 6-month follow-up. The secondary outcome measures are functional exercise capacity, health status, sleep quality, exacerbation rate, and depression and anxiety symptoms assessed at several intervals.

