### Objectives {7}

The overall objective is to assess the effectiveness of the newly developed COPD app as a maintenance program after PR. The primary objective is to assess the clinical efficacy of the COPD app maintenance program on physical activity measured in steps/day in patients with COPD after 6 months. The secondary objectives are to evaluate the effects of the COPD app program on functional exercise capacity, health-related quality of life (HRQoL), patient-reported health status, exacerbations, and depression and anxiety symptoms. Furthermore, we aim to explore patient compliance/adherence and safety, identify factors that facilitate the implementation of the program in the patient’s home setting, and evaluate factors of the program that are especially supportive for the patients.

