### Eligibility criteria {10}

During the recruitment period, all patients with COPD admitted to the PR hospitals will be informed about the ongoing study. Patients who are interested in study participation will receive oral and written information about the study before signing the informed consent for. After signing the informed consent form, participants will be instructed on how to use the activity tracker (Polar A 370) by the local study personnel. Participants will be instructed to wear the activity tracker every day for at least 20 h per day. After the screening period (approximately 8–10 days), eligibility will be judged by the local investigators based on the randomization criteria. If the screening requirements are fulfilled and the participants are deemed eligible, they will be randomized.

Every 2 weeks, an e-link leading to the questionnaires will be sent via email regarding exacerbations (questionnaire defined by the GOLD Guidelines), safety (adverse events or severe adverse events), device deficiencies, and patient feelings. There will be no prohibited medications during the study, and any change in concomitant medications will be noted down biweekly. In addition, at baseline and after 3 and 6 months, another e-link will be sent via email to all participants to complete the CRQ and HADS, to provide instructions to perform the 1-min sit-to-stand test and COPD Assessment Test (CAT), and to evaluate whether participants met their personal goal of physical activity.

Daily steps, sleep efficacy, and total sleep time will be passively collected by a Polar A 370 watch and will be imported to the study-specific electronic case report form (eCRF) system over the Google Fit Server. Figure 1 provides an overview of the study procedures.

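### The adverse event definition takes in COPD exacerbations, which are also a secondary efficacy outcome, and nothing exempts them from the overall between-arm AE test

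*Protocol article*

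**What the plan says.** **What counts as an AE.** The section Adverse event reporting and harms {22} states: "An AE may also consist of a new disease, an exacerbation of a pre-existing illness or condition". It adds: "Medical conditions/diseases present before starting the study are only considered adverse events if they worsen after starting the study". Neither sentence makes an exception for COPD. Trial design {8} and the inclusion criteria restrict the trial to GOLD stages II–IV, so COPD is pre-existing in every participant. Unplanned inpatient treatment makes an event serious, so an exacerbation that leads to admission would be an SAE as well.

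**Exacerbations as an outcome.** The abstract says: "The secondary outcome measures are functional exercise capacity, health status, sleep quality, exacerbation rate, and depression and anxiety symptoms". Objectives {7} repeats this, listing "health-related quality of life (HRQoL), patient-reported health status, exacerbations, and depression and anxiety symptoms" among the secondary objectives. The same section names safety as something to be explored.

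**How the events are collected.** Eligibility criteria {10} describes a two-weekly e-link with items on "exacerbations (questionnaire defined by the GOLD Guidelines), safety (adverse events or severe adverse events), device deficiencies, and patient feelings". Exacerbations and safety events are separate items there.

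**How safety is compared.** The Safety analysis section has all AEs and SAEs described: they "will be described with regards to their severity grade, relationship to the COPD app intervention, and duration". It then gives one inferential sentence: "The occurrence of adverse events and AEs overall between groups will be assessed with a two-tailed" t test after follow-up ends.

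**The concern.** An outcome on which the app is hoped to show a benefit sits, as written, inside the total used to look for harm. This can blur the safety comparison in two ways.

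- **Dilution.** Even if the app has no effect on exacerbations, their patient-to-patient variation adds noise to the AE count. An excess of events that unsupervised home training might cause, such as falls or musculoskeletal or cardiac events, is then harder to see. The exclusion criteria already rule out patients for whom training would be unsafe, so the sponsor has such risks in mind.
- **Offset.** If the app does reduce exacerbations, the overall AE difference moves in its favour and cancels part of any excess of other events.

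In either case, similar overall AE counts would be weak evidence that the training is safe. The issue is which events are counted, and it would remain if another test replaced the t test.

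**Working it through.** **Step 1: the texts side by side.** The harms section makes worsening of a pre-existing disease an AE. The inclusion criteria make COPD pre-existing in all participants. The Safety analysis section compares AEs overall and removes nothing. Read literally, COPD exacerbations are in the tested count. Against that, the two-weekly questionnaire treats exacerbations and safety events as different items, and no section says whether a reported exacerbation is also entered as an AE. The documents leave the point open.

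**Step 2: is there a figure to reproduce?** No. The article gives no AE rate, exacerbation rate, safety alpha or safety power. What follows only illustrates the mechanism.

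**Step 3: inputs.**

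- From the article: 52 per arm (Trial design {8}); two-tailed t test (Safety analysis); 26 per arm remaining after 50% drop-out (Sample size {14}).
- Assumed: alpha 5%; the tested quantity is events per patient over 24 weeks; non-exacerbation AEs are Poisson with mean 0.2 (control) and 0.6 (app); exacerbations are Poisson with gamma frailty of variance 1, with control mean 0.5 or 1.0 and app rate ratio 1.0, 0.8 or 0.6.

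**Step 4: formula.** The variance per patient is m for a Poisson count of mean m, and m + m² with the frailty. With d the difference in means, SE = √[(V_control + V_app)/n], and the power to show more AEs on the app is about Φ(d/SE − 1.96).

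- Without exacerbations: d = 0.4; SE = √[(0.2 + 0.6)/52] = 0.124; Φ(3.23 − 1.96) ≈ 90%.
- With 0.5 exacerbations per patient in both arms: the exacerbation variance is 0.5 + 0.25 = 0.75, so the totals are 0.95 and 1.35. d is still 0.4; SE = √(2.30/52) = 0.210; Φ(1.90 − 1.96) ≈ 48%.

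A simulation of the t test (20,000 replicates, counting significant results in the harmful direction) agrees with the formula:

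| Control exacerbations | App rate ratio | Mean AEs, control vs app | Ratio | Power, formula | Power, simulated |
|---|---|---|---|---|---|
| not pooled | – | 0.2 vs 0.6 | 3.00 | 90% | 91% |
| 0.5 | 1.0 | 0.7 vs 1.1 | 1.57 | 48% | 48% |
| 0.5 | 0.8 | 0.7 vs 1.0 | 1.43 | 32% | 32% |
| 0.5 | 0.6 | 0.7 vs 0.9 | 1.29 | 18% | 18% |
| 1.0 | 1.0 | 1.2 vs 1.6 | 1.33 | 26% | 27% |
| 1.0 | 0.8 | 1.2 vs 1.4 | 1.17 | 10% | 11% |
| 1.0 | 0.6 | 1.2 vs 1.2 | 1.00 | 2.5% | 3% |

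**Step 5: less favourable assumptions.**

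- With 26 per arm: √(0.8/26) = 0.175 gives about 63% without exacerbations, and √(2.30/26) = 0.297 gives about 27% with 0.5 per patient pooled and no app effect on them.
- With a smaller excess, 0.2 vs 0.4, at 52 per arm: √(0.6/52) = 0.107 gives about 46% without exacerbations.
- With 0.5 unrelated AEs in both arms and training-related events of 0.1 vs 0.3: √(1.4/52) = 0.164 gives about 23%, even with exacerbations removed.

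A second set of assumed rates used 0.5 unrelated AEs in both arms, training-related events of 0.1 vs 0.4, and Poisson exacerbations at 0.6 in control. The pooled test detected the excess in 26%, 10% and 2.5% of simulations when the app's exacerbation mean was 0.6, 0.45 and 0.3. A test on non-exacerbation AEs stayed at about 41–42%.

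**The case against.** **The double count is inferred.** The AE definition is generic and permissive, and the questionnaire separates exacerbations from safety events. A reader might infer that every COPD exacerbation is certainly counted twice, but the documents do not say so. What stands is that the definition as written includes them, nothing exempts them, and the sections need reconciling either way.

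**The test sentence is garbled.** It names two quantities that look the same, and one may have been meant as serious AEs. It is therefore not certain that a single pooled test is the only one planned. A separate SAE test would not remove the difficulty, since exacerbations leading to admission would enter it too.

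**Other displays would show the harm.** AEs and SAEs are described by severity, relatedness and duration, and exacerbations are reported as their own outcome. A reader could see fewer exacerbations beside an unchanged AE total. This is a fair point, and it rules out the claim that harm would be hidden altogether. The safeguard is partial. Relatedness to the app is judged by the principal investigator in an open-label trial, and a control patient has no app to which an event could be related, so that table gives no like-for-like comparison of arms. None of the stated summaries is by type of event.

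**This belongs in the SAP.** Tabulation by event type usually does. But the article itself fixes both the AE definition and the between-arm comparison, and the point concerns how those two stated rules combine.

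**Taking exacerbations out has a cost.** Exacerbations provoked by training would leave the tested harm set. This objection is sound. It argues for adding a comparison, and against replacing or demoting the all-AE one.

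**Conclusion.** The point holds in a limited form. As written, the AE definition covers COPD exacerbations, the same events are a secondary efficacy outcome, and the overall between-arm AE comparison does not exempt them. That comparison can be diluted, and partly offset if the app reduces exacerbations, so a null result would not by itself answer the safety question.

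The size cannot be known from the documents. Under the assumed rates, pooling 0.5 exacerbations per patient cuts power from about 91% to about 48% with no app effect on exacerbations at all. All these figures are lower with 26 per arm, and a smaller excess lowers them too. A reader might infer that a real harm would vanish from the comparison. That happens only where the reduction in exacerbations is as large as the excess of other events, for example 1.0 exacerbation per control patient in 24 weeks with a 40% reduction. Nothing in the documents supports expecting that.

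This deserves correction because it is cheap to correct. It does not show that the safety evaluation as a whole fails.

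**What to change.** 1. Reconcile Eligibility criteria {10}, Safety analysis and Adverse event reporting and harms {22} by stating whether COPD exacerbations enter the AE count that is tested. In the same edit, clear up the two quantities named in the test sentence, including whether SAEs are one of them.
2. Add to the Safety analysis section a between-arm comparison of AEs other than COPD exacerbations. Report it beside the all-AE comparison, any SAE comparison and the exacerbation outcome. Keep the all-AE comparison, so that no event leaves view.

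**Cost.** Protocol or SAP wording, one flag per AE and one more table split. The two-weekly exacerbation questionnaire already supplies the information for the flag, so no new data are needed and nothing about treatment or event management changes. Some respiratory events will be borderline and need a rule set in advance. The added test will still have limited power (about 23% in one plausible set of assumed rates), so it should be read with the descriptive tables.
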